## Abstract

**Background:**

Stroke has profound impacts on families. Often, family members, including stroke survivors and the person who takes up the role of the primary caregiver, would encounter demands on finances, rehabilitation arrangement, and even conflicts. Hence, a family-oriented intervention is expected to enable families to rebuild internal and external resources to achieve optimal rehabilitation and community reintegration.

**Objective:**

This study aims to describe a design of a two-tier family-oriented care management intervention for enhancing the family functioning and care capacity of the caregivers of stroke survivors.

**Methods:**

The two-tier care management intervention was guided by a standardized protocol conducted by trained professional care managers (first tier) with the support of trained volunteers (second tier), which lasted for 8-12 weeks. Participants were recruited through collaborating hospitals according to inclusion and exclusion criteria. In order to examine the effectiveness and cost-effectiveness of the two-tier care management intervention, a two-arm randomization multicenter study was designed, including an active comparison group, which was guided by a standardized protocol conducted by trained volunteers. Dyadic participants, including both stroke survivors and their primary caregivers for both groups, were invited to participate in a questionnaire survey using standardized and purposefully developed measures 3 times: before the intervention, immediately after the intervention, and 2 months after the intervention. The primary outcome was family functioning measured by the Family Role Performance Scale and Family Assessment Device-General Functioning Scale. The secondary outcomes included caregiving burden, depressive symptoms, care management strategies, and the incremental cost-effectiveness ratio.

**Results:**

Recruitment began in January 2017 and was completed at the end of April 2019. Data collection was completed at the end of March 2020. As of March 2020, enrollment has been completed (n=264 stroke caregivers). A total of 200 participants completed the baseline questionnaires. We aim to publish the results by mid-2021.

**Conclusions:**

This study successfully developed a two-tier care management protocol that aims to enhance the family functioning of the caregivers of stroke survivors. Guided by a standardized protocol, this family-oriented two-tier intervention protocol was found to be feasible among Chinese families.

**Trial Registration:**

ClinicalTrials.gov NCT03034330; https://ichgcp.net/clinical-trials-registry/NCT03034330

**International Registered Report Identifier (IRRID):**

RR1-10.2196/16703

## Introduction

### Background and Rationale

Stroke has profound impacts on families. In particular, after stroke survivors return home from discharge, they often rely on family members to meet their daily needs for care and support [1,2]. Often, family members, including stroke survivors and the person who takes up the role of the primary caregiver, would be under high stress to face the demands of supporting the activity of daily living, the instrumental activity of daily living, financial and emotional support, rehabilitation arrangement, etc. During this sudden and unexpected caregiving journey, stroke caregivers need to not only equip themselves with knowledge and skills to provide hands-on care on a daily basis but also adjust their roles and functions within the family context. The process of rehabilitation after stroke is often long and challenging, and feelings of frustration, depression, and even family conflicts are common. A study showed that stroke survivor characteristics and family conflicts surrounding recovery was associated with mental distress and physical ill health [3]. In turn, increased psychological distress and poor family function can undermine the stroke survivor’s recovery and rehabilitation process [1,4,5]. Apart from the direct impact of stroke caregivers, poor recovery and rehabilitation of stroke survivors impose a significant financial burden on the health care system [6].

Stroke accounts for 30%-50% of admissions to long-term residential care homes in Hong Kong [6]. Hence, interventions targeting family dynamics are vital. Interventions focusing on primary caregivers revealed the importance of enhancing self-efficacy in reducing the burden and enhancing their well-being at the individual level [7-11]. However, as we argued above, stroke affects the entire family and not only the primary caregivers. Hence, we developed a family-oriented intervention to support families with stroke survivors. A family is the most important social unit that is expected to provide care and support when family members feel sick or ill. When a person experiences a stroke, the family as a whole is affected, and therefore, interventions that enable family functioning as a whole are required.

Research has shown that a volunteer-led community education program successfully improved stroke knowledge [12], indicating that volunteers are untapped resources that can be integrated into interventions. However, studies have shown that a professional-led intervention group produced better outcomes in preventing mood disorders among stroke patients as compared to the volunteer support group [13]. Considering that professional-led and volunteer-led interventions could have unique roles, our research team designed a two-tier care management intervention protocol. In the first tier, trained professionals focused on conducting the assessment, conducting family-oriented interventions such as work-family balance, family communication, and family conference, and assigning and supervising volunteer-led intervention sessions. In the second tier, trained volunteers focused on interventions on enhancing stroke knowledge, enabling exercise, etc. By integrating the two-tier care management intervention, professionals and volunteers could supplement each other to optimize the intervention intensity and to maximize cost-effectiveness.

In summary, our research team developed a two-tier family-oriented intervention that aims to enhance the family functioning of the caregivers of stroke survivors and it has 3 unique features. These features are (1) a family-oriented intervention that focuses on family functioning, (2) a two-tier care management approach consisting of trained professionals (first tier) and trained volunteers (second tier) purposefully designed, and (3) last but not the least, a family-oriented care management intervention, starting from needs assessment, followed by the care plan, implementation, and review.

### Objectives and Hypothesis

The main objective of this 8-12-week randomized controlled trial is to investigate the effectiveness and cost-effectiveness of a two-tier family-oriented intervention in enhancing the family functioning of caregivers of stroke survivors. We hypothesized that a two-tier family-oriented intervention for caregivers of stroke survivors can enhance their family functioning and care capacity as compared to a volunteer-led control intervention.

## Methods

### Study Setting

This is a two-armed, multicenter, double-blind randomized controlled trial (NCT03034330). Stroke survivors and their primary caregivers (up to n=300) were included and randomized in a 1:1 allocation ratio to a two-tier family-oriented care manager–led intervention group (up to n=150) and a volunteer-led control group (up to n=150). In this study, the research team collaborated with 5 local hospitals in the Hong Kong West Cluster, New Territories East Cluster, and New Territories West Cluster and 3 nongovernmental organizations (NGOs) in the Southern, Shatin, and Tuen Mun districts with varied settings. Three on-site teams established the infrastructure to provide direct rehabilitation and support services to stroke patients. The details of the partnering NGOs are listed in Table 1.

**Table 1 table1:** Details of the study sites.

District	Setting	Services
Southern	District Elderly Community Centre	Providing support services to healthy, vulnerable, and frail older adults living in the community and family caregivers
Shatin	Home Support Team of the Integrated Discharge Support Program for Elderly Patients	Providing postdischarge support services for older adult patients, such as meal delivery, household cleaning, home assessment, and modification
Tuen Mun	Community Rehabilitation Day Centre	Providing both professional and psychosocial rehabilitation services to discharged patients with stroke, neurological, or physical impairments

### Ethical Approval

We obtained ethical approval from the Institutional Review Board of The University of Hong Kong/Hospital Authority Hong Kong West Cluster (UW 16-1019), The Joint Chinese University of Hong Kong-New Territories East Cluster Clinical Research Ethics Committee (2016.679-T), and New Territories West Cluster Research Ethics Committee (NTWC/CREC/16123). The clinical trial was registered at the United States National Institutes of Health (clinicaltrials.gov; NCT03034330). Informed written consent was obtained from all participants included in the study. This study started in June 2016 and ended in March 2020.

### Inclusion Criteria

All caregivers of stroke survivors identified by the NGOs or referred by the hospitals were recruited if they (1) were Cantonese-speaking adults aged 18 years or older, (2) had a family member who had a stroke (ischemic or hemorrhagic stroke) at the age of 18 years or older, (3) provided care or were with a stroke survivor for no less than 10 hours per week (including time supervising a domestic helper) after discharge from the acute hospital, and (4) reported significant caregiver burden (a score ≥6 using the four-item Zarit Caregiver Burden Interviews [14]), depressive mood (a score ≥2 using the Patient Health Questionnaire-2 [15]), or family dysfunction (a score ≥6 using 4 items selected from the Family Caregiver Conflict Scale [FCCS] for Stroke [16]). These 3 parameters were chosen because this study aims to enhance the family functioning and care capacity of stroke caregivers. The inclusion criteria for stroke survivors were (1) being a Cantonese-speaking adult aged 18 years or older, (2) having a family caregiver participating in this study, (3) being able to communicate with interventionists and interviewers, and (4) being competent to provide written informed consent.

### Exclusion Criteria

Caregivers were excluded if they were diagnosed with Alzheimer disease or other types of dementia (clinically diagnosed), or were suffering from acute health conditions (eg, conditions caused by a virus, infection, injury, misuse of drugs or medication) that prevented them from providing caregiving support. As this intervention involves strong engagement and commitment from caregivers, people with cognitive impairments are not suitable for this study. Acute health conditions include cancers and other major illnesses such as stroke and a broken bone that negatively affect the caregivers’ physical and mental conditions, which prevented them from providing caregiving or joining the intervention. Stroke survivors (1) who had a transient ischemic attack without a major ischemic or hemorrhagic stroke, (2) whose family caregiver refused to participate in this study, (3) who were not able to communicate with interventionists and interviewers, or (4) who were not competent to give written informed consent (eg, illiterate or with cognitive impairment) were excluded from this study.

### Sample Size Calculation

We used the G*Power 3 software (Psychonomic Society, Inc) to determine the minimum sample size required for obtaining a significant medium effect size of family functioning, given α=.05 and statistical power of 0.80, with a two-sided significance of .05. While we estimated the sample size, we could only take references from similar relevant studies reported in the literature that were available. References were taken from studies using individual-based outcomes such as the readmission rate of stroke survivors [17], depressive symptoms of caregivers [18], family role performance [19], and caregiver burden [4]. We admit that this is a limitation of our study. Based on a previous study, readmission rates within 6 months after discharge were significantly lower among patients who received follow-up home visits (26%-34%) compared to those who received standard aftercare only (44%) [17]. Besides, stroke accounts for 30%-50% of admissions to long-term residential care homes in Hong Kong [6]. To the best of our knowledge, since no intervention has utilized both care managers and volunteers in providing support to stroke families, we hypothesize that our designed intervention will lower the readmission rates of stroke survivors. As per this, we hypothesized that 15% of the stroke survivors whose caregivers were in the intervention group will be readmitted to a hospital or admitted to a residential care facility within 6 months after discharge, whereas 30% of the stroke survivors whose caregivers were in the control group will be readmitted to a hospital or admitted to a residential care facility over the same period. The resulting sample size estimate was 140 dyads per group; however, to ensure a sufficient effect size, and considering attrition, a sample size of 150 dyads per group will be used. We estimated that the attrition rate will be 25% based on the risk of second stroke occurrence within 1 year [20] as well as the fact that the previous intervention study lasted for around 6 months [17].

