## Results

The clinical trial began recruiting in January 2017, and recruitment was completed at the end of April 2019. Data collection and data set construction were completed at the end of March 2020. As of March 2020, enrollment has been completed (n=264 stroke caregivers). A total of 200 participants completed the baseline questionnaires. We aim to publish the results by mid-2021. The intervention protocol is in Traditional Chinese only and is available upon request from the corresponding author.

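### The 140 dyads per group come from a readmission endpoint, not from the family-functioning outcome named as the target, and raising them to 150 does not cover the stated 25% attrition

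*Protocol article*

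**What the plan says.** All the planning figures stand in one section of the protocol article, Sample Size Calculation.

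- Target: the software was used for the "minimum sample size required for obtaining a significant medium effect size of family functioning".
- Error rates: "given α=.05 and statistical power of 0.80, with a two-sided significance of .05".
- Effect put into numbers: "we hypothesized that 15% of the stroke survivors whose caregivers were in the intervention group will be readmitted to a hospital" or admitted to residential care within 6 months of discharge, "whereas 30% of the stroke survivors whose caregivers were in the control group will be readmitted to a hospital" or residential care over the same period.
- Result: "The resulting sample size estimate was 140 dyads per group".
- Allowance for loss: "considering attrition, a sample size of 150 dyads per group will be used. We estimated that the attrition rate will be 25" per cent.

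The section says that its references were individual-level outcomes and calls this a limitation. The Abstract and Table 3 give the primary outcome as family functioning, measured by the Family Role Performance Scale and the FAD-GF. Hospital and residential admissions belong to the service-use data, which Table 3 lists as secondary. On achieved numbers, Results states that "enrollment has been completed (n=264 stroke caregivers") and that 200 participants completed baseline questionnaires.

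**The concern.** The section names one target and gives figures for another. A reader who stops at the opening sentence will believe that the trial was sized for family functioning. No effect size, standard deviation or sample size for family functioning appears anywhere in the article.

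The attrition allowance also disagrees with itself within two consecutive sentences. Ten extra dyads on 140 cannot absorb a 25% loss.

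The stated power of 0.80 is the trial's only published statement of sensitivity. It may not hold for the endpoint it was computed on, and it says nothing about the outcome that the trial is meant to test.

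**Working it through.** **Inputs, all from Sample Size Calculation:** event rates p1 = 0.15 and p2 = 0.30; two-sided alpha 0.05; power 0.80; 140 per group before loss; 150 per group planned; attrition 25%.

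**1. Reproducing 140.** With mean rate 0.225, the usual two-proportion formula is

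n = [1.96·√(2·0.225·0.775) + 0.8416·√(0.15·0.85 + 0.30·0.70)]² / 0.15²
= [1.96·0.5906 + 0.8416·0.5809]² / 0.0225 = 120.5, so **121 per group**.

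With continuity correction it is 133.5, so **134 per group**. The unpooled form gives 118 and the arcsine form 119. A power of 0.85 without correction gives 138, the closest match, but the section states 0.80. So 140 is not reproduced exactly. It is larger than any of the 0.80-power figures, so the difference is on the safe side.

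**2. Does 140 come from a medium effect on family functioning?** The article gives no number for medium. Taking d = 0.5 as an assumption, a two-sample t test needs 63.8, so 64 per group. That is not 140. The figure therefore belongs to the readmission comparison, as the order of the sentences suggests.

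**3. Attrition.**

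- Loss covered by going from 140 to 150: 1 − 140/150 = **6.7%**.
- Number needed to keep 140 after 25% loss: 140/0.75 = 186.7, so **187 per group**.
- Left from 150 after 25% loss: 150 × 0.75 = 112.5, about **112 per group**.
- From the recomputed bases: 121/0.75 gives 162 and 134/0.75 gives 179. Both also exceed 150.

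**4. Power for 15% against 30%, two-sided 0.05.** The z-test power is Φ{[0.15·√n − 1.96·0.5906] / 0.5809}. At n = 112 this is Φ(0.740) = 0.770.

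| Dyads per arm with the endpoint | z test | Fisher exact |
|---|---|---|
| 150 (plan, no loss) | 0.88 | 0.85 |
| 112 (plan, 25% loss) | 0.77 | 0.73 |
| 132 (264 enrolled, equal arms assumed, no loss) | 0.84 | 0.80 |
| 99 (264 enrolled, equal arms assumed, 25% loss) | 0.72 | 0.66 |

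**5. The primary outcome at the same numbers** (two-sample t test, two-sided 0.05). The standardised difference detectable with 80% power is about 0.38 at 112 per arm and 0.40 at 99 per arm. If d = 0.5 is assumed, power is 0.96 and 0.94. The requirement would be 64 evaluable per arm, or 64/0.75 = 85.3, so 86 with 25% attrition. If alpha were split over the two primary scales (0.025 each), about 78 evaluable per arm would be needed.

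**The case against.** The strongest reply is that the 25% need not apply to this endpoint. Under Service Utilization Record, the article retrieves service-use data from the Hospital Authority's electronic system until 6 months after the second follow-up. Statistical Analysis includes every randomised participant. A caregiver who stops answering questionnaires need not take the survivor's admissions out of the data. Part of the basis for the 25% is second stroke, which would often itself be a readmission and so an event rather than a missing value. This stands, and it makes the power loss conditional. It is not a full answer, because the section itself applies the 25% to this calculation and residential admission may depend partly on questionnaires.

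It can also be said that the authors admit to relying on individual-level outcomes. They do, but that does not tell the reader that the target in the opening sentence was never given a number.

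Some stronger readings are tempting but not supported:

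- **That the trial is too small for its primary outcome.** At an assumed d = 0.5, the planned and enrolled numbers are more than enough even after 25% loss.
- **That 140 is an error that weakens the trial.** It exceeds the 121 or 134 needed, and an article need not show the software options.
- **That 15% contradicts the 26%–34% cited for home-visited patients.** The control arm here also receives home visits, and its assumed 30% lies inside that range. The 15% is put forward as a hypothesis for a new intervention.
- **That 25% should also be taken off the 200 with baseline data.** From 264 to 200 is already a loss of 24.2% (64/264), so this would probably count attrition twice.
- **That the endpoint cannot be measured at all.** A window of 6 months from discharge is workable for dyads referred by hospitals. It is a problem only for those from the NGOs' existing users who enrol late after discharge, and their share is not stated.

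**Conclusion.** The point holds in a limited form. The section states one target and sizes another, and its allowance for attrition is wrong on its own three figures: 150 covers 6.7% loss from 140, not 25%. Neither statement depends on any outside figure.

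The effect on power depends on how many dyads lose the readmission endpoint. At 150 per arm it runs from 0.73–0.77 with 25% loss to 0.85–0.88 with none, so the stated 0.80 fails under the section's own attrition figure but not if records capture every dyad. Sensitivity for family functioning is unstated rather than shown to be poor. The figures for it rest on a two-sample t test, and the rows based on 264 enrolled assume equal arms. It is worth correcting because the stated power is the only one the article offers and restating it is cheap.

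**What to change.** Recruitment and data collection are finished, so the change is to the text, with no extra enrolment.

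1. State that 140 per group was derived from readmission or residential admission, and label that endpoint secondary.
2. Withdraw the claim that 150 allows for 25% attrition from 140.
3. Give readmission power as a range by endpoint loss: about 0.73–0.77 with 25% loss and 0.85–0.88 with none, at 150 per arm. Say how far the electronic records capture the endpoint after dropout, and how the 6-month window is handled for dyads enrolled late after discharge.
4. For family functioning, do not write a new planning rationale after the fact. Report the detectable standardised difference at the evaluable number: about 0.38 at 112 per arm and 0.40 at 99 per arm, for 80% power at two-sided 0.05. If d = 0.5 is quoted as medium, mark it as an assumption and give the alpha used: 64 evaluable per arm at 0.05, or about 78 if alpha is split over the two primary scales.

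The cost is a few sentences. The readmission claim becomes weaker or conditional, and the primary outcome gains the statement of sensitivity that it lacks.

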### Screening, Randomization, and Intervention Allocation

Stroke survivors and their primary caregivers were first to be identified by physicians in the abovementioned 5 hospitals. Potential dyads were referred to the 3 NGOs using a standardized referral form developed by the research team. Stroke survivors and their primary caregivers were also identified from the pool of existing service users of the 3 NGOs. The care team consisted of trained social workers from the 3 NGOs who performed screening using a standardized screening form that comprised data on demographics, family functioning, caregiving burden, depressive symptoms, and willingness to join. Participants were recruited if they met the inclusion criteria, passed at least one threshold in the areas of family functioning, caregiving burden, or depressive symptoms, and showed a willingness to join.

After recruitment, trained social workers from the 3 NGOs notified the research team to conduct randomization. To avoid bias and to ensure an equal number in each group within each study site, group allocation was determined using computer-generated block randomization with a block size of 4 by using SPSS Statistics (version 23.0, IBM Corp). A member of the research team informed the care managers about the subject code for group allocation. The participants and researchers were blinded to the group assignment. The care managers and volunteers were not blinded to the group assignment, because they needed to know the participants’ group assignment to provide interventions.

Upon randomization, trained care managers were assigned to different cases by the NGOs’ internal control while 2-3 trained volunteers were assigned to the same group depending on their availability and gender. The research team was cautious about the gender of the volunteers; female caregivers may find it difficult to face many male volunteers due to traditional values, while male caregivers may be more willing to receive support from male volunteers.

Three strategies were adopted to ensure that the intervention and control groups were separated throughout the study. First, both interventions were guided by a standardized protocol conducted by the trained interventionists independently. Second, interventions were home-based, which prevented participants from meeting with each other during the intervention period. Last but not the least, the research team served as a safe guide during the monthly field visit to secure protocol compliance.

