### Statistical Analysis

We will use descriptive statistics to present baseline characteristics and outcome measures, and we will transform any skewed variables and correct their skewness before inferential analysis. To assess normality, we will perform the Shapiro-Wilk test of normality as well as the normal Q-Q Plot, while we will use the Wilcoxon signed-rank test for the nonparametric test. We will also perform the chi-square or independent two-tailed *t* tests to examine the differences in the baseline characteristics between the intervention and control groups. For the primary and secondary outcomes, we will perform a multi-factor analysis of variance or general linear model to compare the differential changes in each outcome across the 3 assessment time points, that is, T0, T1, and T2 between the 2 treatment groups. This model can account for repeated measures data that are intercorrelated and that produce unbiased estimates even in the presence of the missing data, provided that the data are missing at random. Multivariate regression will be used to compare the differences in the outcomes between the 2 treatment groups and will control for the effect of potential covariates such as depressive symptoms and caregiver burden. Recruitment rate, attrition rate, and missing data will also be examined and reported. All outcome measures will be analyzed based on intention-to-treat principles. Every participant who is randomized according to the randomized treatment assignment will be included. This method of analysis preserves the prognostic balance afforded by randomization [25]. The cost of study participation, including staff cost, travel expenses, and program materials, will be expressed in Hong Kong dollars. All the statistical analyses will be performed using SPSS Statistics. All statistical tests will be two-sided with the level of significance set at .05.

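### Randomisation is balanced within site, but site is not named in the analysis models: a modest, avoidable loss of precision in between-group score comparisons, and none in the group-by-time contrast unless change differs by site

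*Protocol article*

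**What the plan says.** Under Study Setting, the protocol article describes a 1:1 trial run with "3 nongovernmental organizations (NGOs) in the Southern, Shatin, and Tuen Mun districts with varied settings". Table 1 lists them as an elderly community centre, a post-discharge home support team and a community rehabilitation day centre.

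Under Screening, Randomization, and Intervention Allocation, "group allocation was determined using computer-generated block randomization with a block size of 4", and the stated purpose is partly "to ensure an equal number in each group within each study site". The word stratified does not appear, but equal numbers within each site can be assured only by blocking separately by site.

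Under Statistical Analysis, the model for primary and secondary outcomes is given as "we will perform a multi-factor analysis of variance or general linear model to compare the differential changes in each outcome". The only factors named for it are assessment time (T0, T1, T2) and treatment group. A further regression compares outcomes between the groups and "will control for the effect of potential covariates such as depressive symptoms and caregiver burden". Tests are two-sided at .05. Site is not named there as a factor, stratum, covariate or random effect.

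**The concern.** When arms are balanced within site, differences between sites in the level of an outcome cannot contribute to the difference between arms. A model without site still counts those differences as residual noise. Its standard error then exceeds the real sampling variability of the estimate, the test rejects less often than .05 under the null, and some of the precision bought by blocking is lost.

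The sites offer different services to different clients, so outcome levels may differ between them. Precision is also not in surplus: up to 300 dyads were planned, and the Results section reports 264 caregivers enrolled and 200 participants with baseline questionnaires.

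**Working it through.** **Inputs from the protocol article.** Three sites; 1:1 allocation; blocks of 4 within site; two-sided .05; assessments at T0, T1 and T2; 200 participants with baseline data (about 100 per arm). The article states no site variance and no standard error, so there is no plan figure to reproduce on this point. Its sample size of 140 dyads per group rests on readmission proportions and does not enter here.

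**Assumptions.** The site share of total outcome variance, written r, is taken from 0.01 to 0.20. The power illustration uses an effect of 0.4 SD with 100 per arm.

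**1. Comparison of scores between groups (T1 or T2).** With total variance 1 and arms balanced within site, the true variance of the arm difference is (1 − r) × 2/n. A model without site reports about 2/n. The reported standard error is therefore too large by 1/sqrt(1 − r), and the effective two-sided level is 2 × [1 − Φ(1.96/sqrt(1 − r))].

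| r | SE too large by | Effective critical value | Type I error, formula | Type I error without site, simulated |
|---|---|---|---|---|
| 0.01 | 0.5% | 1.970 | 0.049 | – |
| 0.02 | 1.0% | 1.980 | 0.048 | – |
| 0.05 | 2.6% | 2.011 | 0.044 | 0.041 |
| 0.10 | 5.4% | 2.066 | 0.039 | 0.039 |
| 0.20 | 11.8% | 2.191 | 0.028 | 0.026 |

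The simulation used 198 participants, three equal sites, exact within-site balance, no treatment effect and 3,000 runs. With site in the model, type I error was 0.046 to 0.048. The Monte Carlo error near .05 is sqrt(0.05 × 0.95/3000) = 0.004, so formula and simulation agree.

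**2. Power for the same comparison.** The standardised effect on the total SD is 0.4/sqrt(2/100) = 2.828. A calculation that ignores site altogether gives Φ(2.828 − 1.96) = 0.807. Under blocked allocation, the test without site does slightly better than that, because the estimate varies less than its standard error implies: Φ((2.828 − 1.96)/sqrt(1 − r)). With site in the model, power is Φ(2.828/sqrt(1 − r) − 1.96).

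| r | Site omitted | Site included | Loss |
|---|---|---|---|
| 0.01 | 0.809 | 0.811 | 0.002 |
| 0.05 | 0.814 | 0.827 | 0.013 |
| 0.10 | 0.820 | 0.846 | 0.026 |
| 0.20 | 0.834 | 0.885 | 0.051 |

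**3. Change from baseline (the T1 part of the group-by-time contrast).** A site effect that is the same at T0 and T1 cancels in T1 − T0. In the simulation, with a within-site correlation of 0.5 between times, the model standard errors were:

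| r | Site-by-time variance | Site omitted | Site included | Type I error, omitted |
|---|---|---|---|---|
| 0.05 | 0 | 0.1381 | 0.1381 | 0.052 |
| 0.10 | 0 | 0.1349 | 0.1349 | 0.050 |
| 0.20 | 0 | 0.1270 | 0.1269 | 0.051 |
| 0.10 | 0.05 | 0.1386 | 0.1349 | 0.045 |

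The last row is the only one with a loss: 0.1386/0.1349 = 1.027, about 3%. Algebra gives the same. The change variance is 0.90 without and 0.95 with the site-by-time part, and sqrt(0.95/0.90) = 1.027.

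**The case against.** A reader might infer that every stated analysis has inflated standard errors. The documents do not support that. The model given for primary and secondary outcomes is there "to compare the differential changes in each outcome across the 3 assessment time points". In that contrast each caregiver is her own control, and the differences that Table 1 makes plausible are differences in level, which cancel. This objection stands. It also means that a site main effect alone would leave the group-by-time test as it is.

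Cancellation does require the site effect to be constant over time, and the article gives some reason for doubt. T0 was collected by care managers or volunteers, who came from the NGOs, whereas T1 and T2 were collected by a trained research assistant. A site-specific assessor effect at T0 would not cancel. How large it might be is unknown.

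A reader might also infer that the models exclude site. They do not: the analysis of variance is called multi-factor, and the covariates are given as examples. Site is unnamed, and a fuller analysis plan may name it. Still, the section does go as far as naming factors and example covariates, and the one variable that the allocation was built on is not among them.

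Three further points limit the size. The site share is an assumption, and all caregivers enter through the same thresholds for burden, depressive mood or family dysfunction, which may narrow site differences. Covariates in the regression may absorb part of any site difference. Families sharing one of the nine care managers would push standard errors the other way, so the net direction of error in the reported tests cannot be read from the omission of site alone.

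**Conclusion.** The point holds in a limited form. Site is the balancing factor in the randomisation and is not named in the stated models. For between-group comparisons of scores, omitting it makes standard errors conservative by about 0.5% to 12% over assumed site shares of 1% to 20%. Under the illustrative 0.4 SD effect with 100 per arm, power falls by between 0.002 and 0.051. At the low end this is negligible. For the group-by-time contrast there is no loss from constant site differences, and about 3% at an assumed site-by-time variance of 0.05.

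The consequence is a modest loss of efficiency. The documents do not support a reading that the treatment estimates are biased, that false positives are inflated by this omission, or that the principal analysis is invalid. The severity is minor.

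**What to change.** State in the Statistical Analysis section that study site (three levels, fixed effect) is included in the between-group regression, and that site and site-by-time are included in the repeated-measures model, for all primary and secondary outcomes, because allocation was balanced within site.

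The cost is one sentence and a few degrees of freedom: 3 − 1 = 2 for site and (3 − 1) × (3 − 1) = 4 for site-by-time. No new data are needed, since site is known for every family from the randomisation. Adjustment would also help if the participants without baseline data (264 − 200 = 64, if both counts refer to caregivers) have upset the within-site balance among those analysed.
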